#### Trial design

The Consolidated Standards of Reporting Trials (CONSORT statement 2010) for RCT’s of non-pharmacological treatments will inform this single blind randomised placebo-controlled trial with a matched pair design [65]. Matched pair designs are recommended to reduce covariate effects and strengthen comparisons between groups [66]. Children will be matched on age and composite score [36] on the sense©_assess *Kids* [56]. There will be two arms of this study, *Sense*© *for Kids* training and a dose matched Goal Directed Training via Home Program (Fig. 1). Children will be randomised following baseline assessment to one of these treatment groups. The children in the S*ense*© *for Kids* training group will receive two therapist-directed one-hour treatment sessions per week for six weeks, plus a third hour per week of *Sense*© *for Kids* occupational training carried out by the primary caregiver (who will receive coaching and guidance from the therapist). Children in the Goal Directed Training via Home Program will receive one hour a week of therapist led Goal Directed Training and will undertake a further two hours per week of home practice with primary caregiver support. Differences in therapist directed therapy time exists between these two interventions and reflect the nature of each intervention. The total dose of therapeutic activity is equal.

**Fig. 1 Fig1:**
[figure not shown]
Study design with assessment schedule. Footnote: This figure illustrates the study design and assessment timepoints. Assessment 1 = baseline, assessment 2 = post 6 weeks of intervention, assessment 3 = 6 week follow-up, assessment 4 = 6 month follow-up and assessment 5 = 12 month follow-up. Assessments carried out at each time-point are detailed in Table 2

#### Recruitment

Children will be recruited through the cerebral palsy mobility service at Perth Children’s Hospital, a large state-based tertiary centre.

#### Participants

##### Inclusion criteria

This study will include school aged children and youth:With a paediatrician confirmed description of HCPAged 6–15 yearsWho can follow assessment procedure (including fMRI)With a confirmed impairment in somatosensory discrimination function as assessed on the sense©_assess_*Kids.*Who live within metropolitan Perth, Western Australia

##### Exclusion criteria

This study will not include children and youth who have:Upper limb surgery in the 12 months preceding baseline assessmentsMRI contraindications including: metal implants, implantable devices, significant anxiety issues, claustrophobia, or behavioural problems

For children in receipt of Botulinum toxin-A for spasticity management, study commencement will begin 12 weeks after their most recent treatment to allow for Botulinum toxin-A “washout”.

#### Withdrawal

Children and their families are free to withdraw at any time. Any data collected prior to withdrawal will be retained and used for an intention-to-treat analysis.

#### Allocation

Minimisation will be employed to optimise the homogeneity of the two groups [67]. Children will be matched for age (± 6 months) and somatosensory discrimination capacity composite score (mild/moderate/severe). When a child is enrolled to the study without a match for age and somatosensory capacity, that child will be randomly allocated to a treatment group using an online randomisation form by a staff member not otherwise involved in the study. The next child enrolled who is a match for the unmatched participant will be automatically allocated to the alternate group. The process will be repeated for each matched pair; the first member always being allocated at random.

#### Blinding

The families and *treating* therapist(s) will not be blinded to group allocation, but families will be blinded to the study hypotheses. The therapist(s) responsible for *assessment* will be blinded to group allocation. If blinding is broken, this will be noted in the therapist’s treatment or assessment record and reported, where possible a new assessor will be allocated to the participant where unblinding has occurred. To protect the blinding of assessors, participants will be coached not to discuss group allocation with assessors, and interventionists will not discuss study hypotheses with participants.

#### Sample size

To determine the sample size required for this study we used pilot data from seven children with HCP who received the *Sense*© for_Kids intervention [47]. Data from the Wrist Position Sense Test (a component of the sense©_assess_*Kids*, see below) were entered into G* Power [68] and a two tail “Means: difference between two independent groups” power calculation was performed. With an intervention group mean of 15.94 and standard deviation 9.72; and control group mean 25.79 and standard deviation 11.93 the calculated effect size was 0.9052. To detect this effect size, we need 42 subjects (21 in the intervention group and 21 in the control group) to have statistical power of 0.8 at the significance of 0.05. To account for attrition, this study will aim to enroll 50 children, with 25 in each of the control and intervention groups.

#### Retention

Participant retention will be promoted through access to a consistent contact person to address any queries and for coordinating assessment and intervention sessions. As far as possible the booking of assessment and intervention sessions will be flexible to meet participant needs.

#### Study protocol

All outcomes will be measured within two weeks prior to commencement, again within two weeks following completion of intervention, then six weeks, six months and 12 months’ post intervention (± 2 weeks; Table 2). Assessment and intervention will take place in children’s homes or at school, whichever is the most convenient for families, except for MRI assessments which will take place at Perth Children’s Hospital. MRI data will be acquired at all time points, except the 6 weeks follow up.

Table 3 outlines when each outcome measure will be obtained. Time point one is the baseline assessment, time point 2 is at completion of 6 weeks of intervention, time point 3 is 6 weeks’ post intervention completion follow-up, time point 4 is 6 months post intervention completion follow-up and time point 5 is the 12 month post intervention completion follow-up.

**Table 3 Tab3:** Outcome measures

Outcome measure	Time Point					ICF Domain
	1	2	3	4	5	
Sense©_assess_*Kids*	•	•	•	•	•	Body structure/function
Magnetic Resonance Imaging	•	•		•	•	Brain structure/function
Assisting Hand Assessment	•	•	•	•	•	Activity
Goal Attainment Scaling	•	•	•	•	•	Activity and participation
Canadian Occupational Performance Measure	•	•	•	•	•	Activity and participation

### Outcome measures and procedure

#### Body function and structure

##### Sense©_assess_Kids

The sense©_assess_*Kids* [69] is a suite of tests which measure functional somatosensory discrimination ability. The domains of somatosensation measured by the sense©_assess_*Kids* include the Protective Touch Test [70, 71], the Tactile Discrimination Test [72], the functional Tactile Object Recognition Test [73] and the Wrist Position Sense Test [74]. The Protective Touch Test uses the 4.56 Semmes Weinstein monofilament to test tactile registration at the threshold of protective touch. The Tactile Discrimination Test is a forced choice test of tactile discrimination whereby children need to indicate in a series of presentations which surface out of three is different. The functional Tactile Object Recognition Test is a 14-item test of haptic object recognition with multiple versions in which children are presented with familiar and novel objects out of vision and indicate what they are exploring using a response poster with pictures of all possible items. The Wrist Position Sense Test is a measure of proprioception in which a child’s hand is moved out of vision to 20 positions in random order in the flexion/extension plane of movement of the wrist using a lever and a protractor scale Children indicate where their hand is positioned using a protractor scale immediately above their occluded hand. The sense©_assess_*Kids* has high reliability and normative standards for typically developing children aged 6–15 years [75], and demonstrated construct validity and clinical acceptability for children with CP aged 6–15 years [56, 76].

##### Magnetic resonance imaging

Quantification of central neural change in response to intervention contributes to the understanding of the mechanisms that lead to sustained functional improvements. In this trial, we aim to quantify brain changes that accompany any clinical improvements. To this end, we intend on analysing three types of MRI: *structural MRI*, task-based *functional MRI* (fMRI), and *diffusion MRI* (dMRI).

MR imaging will be conducted on a 3 Tesla Siemens Magnetom Skyra scanner (Siemens, Erlangen, Germany) located at the Perth Children’s Hospital (PCH), Nedlands, Western Australia. Scan types are listed in Table 4 and detailed below. Prior to the initial scan each child will attend an MRI preparation session. This has been demonstrated to improve the success of sedation-free brain MRI scanning in children [77]. The preparation session will include watching a presentation about the MRI experience, familiarisation with the fMRI task (see below) and practice in a mock MRI scanner. On each arrival at the PCH Radiology Department for MRI scans children will be familiarised with the scanning procedure, scanning devices, and receive 5–10 min of practice of the fMRI task. Following the MRI, participants will complete a simple questionnaire regarding the MRI experience including awareness of the stimuli, degree of concentration and comfort.

**Table 4 Tab4:** MRI scans to be acquired at each of the four time points

	Type	Resolution	Additional Details
T1 MPR	Structural	1 mm iso	3D
T2 FLAIR	Structural	1 mm iso	3D
T2 Blade	Structural		
GRE	field map	3 mm iso	for EPI distortion correction
EPI	Functional	3 mm iso	80 frames
EPI	Diffusion	2 mm iso	8× b = 0 s/mm^2^ 20× b = 1000 s/mm^2^ 60× b = 3000 s/mm^2^

Abbreviations. *MPR* Multiplanar Reformatting, *FLAIR* Fluid Attenuation Inversion Recovery, *GRE* Gradient Echo, *EPI* Echo Planar Imaging

##### Structural MRI

Both high resolution T1 and T2 images will be acquired (see Table 3). The participant will be able to watch a DVD of choice during anatomical sequences. Anatomical reporting will be conducted upon these images by a paediatric neuroradiologist. Baseline MRIs will be classified using the harmonized classification of magnetic resonance imaging, based on pathogenic patterns (MRI classification system or MRICS) proposed by the Surveillance of CP in Europe network [78]. MRI Classification will be documented for each participant and utilised for subgroup data analysis. A paediatrician will meet with the participant and their caregiver to discuss anatomical findings and the primary treating physician will be informed of these results.

##### Functional magnetic resonance imaging

Functional Magnetic Resonance Imaging will be utilised as an indirect measure of neuronal activation in the brain in response to a somatosensory stimulus. Functional MRI utilizes blood-oxygen-level-dependent (BOLD) contrast to indirectly measure neuronal activation in the brain. In neurorehabilitation, fMRI has been utilised to identify, quantify and map cortical activation associated with execution of particular tasks [15]. Functional MRI has also been used in research as a physiological marker of brain plasticity in children with cerebral palsy, and small studies of motor function in children with CP have demonstrated a significant change in task related cortical activation following constraint-induced therapy [79, 80]. Correlation between somatosensory functional impairment post-stroke and central neural changes has been demonstrated using fMRI [36, 81].

Pre-intervention, fMRI activation patterns in response to somatosensory stimulation of both hands will be measured as a baseline, with focus on cortical somatosensory processing centres including primary somatosensory cortex (S1) and secondary somatosensory cortex (S2). Post-intervention fMRI somatosensory task-related activation will be measured and compared to pre-intervention results as an indicator of central neural change in response to therapy. This methodology is supported by literature that indicates that in order to measure neuroplasticity with fMRI, scans should be obtained during a task, both before and after intervention, for at least 20 people per experimental group [82].

In conjunction with the CSIRO, Florey Institute of Neurosciences and Mental Health and La Trobe University, an fMRI protocol [37, 81] has been adapted for use in children with CP. This protocol consists of two acquisitions – one per hand. Each scan will consist of four 30-s ‘touch discrimination’ blocks, each preceded by a 30 s rest block. During touch discrimination blocks, a device is used to present a textured grid to the fingertips in a manner controlled for speed and pressure, alternated with no stimulus. A plastic texture grating is moved side to side across the fingertips of the second, third and fourth digits [37, 81]. Within block, two different plastic texture grids will be delivered, with spacings of 1500 and 3000 μm between the gratings, alternating every five seconds. These texture grids will be presented in a different alternating order every block to maintain attention of the participant. Participants will be instructed to feel and pay attention to the differences between the two textures presented in each block, but to remain still. A screen showing the words ‘FEEL’ or ‘REST’ will be shown to the participant during these respective blocks to cue attending to the stimuli. The pressure of stimulus delivery is calibrated at the commencement of the scan via a weighted pulley system. To control for movement, the participant’s hand rests on a platform with custom openings for the fingertips and is immobilised in the device as the stimulus is moved from side to side under the fingertips. The control ‘REST’ condition of the paradigm is no presentation of the textured grid to the participant’s fingers, though it continues to be moved at a constant speed to the side of the participant’s hand [37, 81]. The participant lies supine throughout.

##### Diffusion magnetic resonance imaging

Diffusion magnetic resonance imaging (dMRI) will be used to investigate brain microstructural changes within pathways delineated using fMRI driven diffusion tractography. dMRI data will be acquired using a multi-shell approach, which includes 8 non-diffusion weighted images, 20 diffusion weighted images at b = 1000s/mm^2^, and 60 diffusion weighted images at b = 3000 s/mm^2^. Correction for susceptibility distortions will be performed using reverse phase-encoded non-diffusion weighted images. Fibre orientation distributions for tractography will be estimated using multi-shell multi-tissue constrained spherical deconvolution [83] implemented in MRtrix software. Fractional anisotropy (FA) will be estimated based on the b = 1000s/mm^2^ shell.

### Activity

The *Assisting Hand Assessment* (AHA) [57] and the *Adolescent Assisting Hand Assessment* (Ad-AHA) [84] are measures of how a child with HCP or brachial plexus palsy uses their involved hand for bimanual activity. The AHA has been found to have good construct validity, excellent test-retest reliability (0.99) and is responsive to change when used to assess children aged 18 months to 12 years [85]. The Ad-AHA utilises the same scoring components as the AHA and has excellent intra-rater (0.97) and test-retest (0.99) reliability [86]. The assessments are conducted as a play session and are video recorded for scoring at a later time [57, 84].

The *Canadian Occupational Performance Measure* (COPM) [59] is a measure of a client’s self-perceived occupational performance over time. The COPM has been found to have good validity and reliability and is responsive to change [87] and has been found to have moderate reproducibility [88].

*Goal Attainment Scaling* (GAS) [58] is a technique used to quantify goals set in a rehabilitation setting. This goal setting technique enables the conversion of measurable goal attainment on a 5-point scale into t-scores which are normally distributed around a mean score of 50 and a standard deviation of 10. The GAS has been found to be a valid and reliable measure of goal attainment [89] with excellent inter-rater reliability (>.90) and satisfactory concurrent validity [90].

### Descriptive measures

To describe our population the following scales and measures will be completed at baseline.

The *Gross Motor Function Classification Scale- Expanded and Revised* (GMFCS-E&R) [91] is a five level scale describing gross motor function for children with cerebral palsy aged 6–12 years and 12–18 years. The GMFCS describes a range of abilities from level I, where children are independently mobile, through to level V where children have limited ability to maintain head and trunk postures and are dependent on wheeled mobility with assistance from others [91].

The *Manual Ability Classification Scale* (MACS) [92] is a five level scale describing the ability of children with cerebral palsy aged 4–18 years to handle objects in everyday activities. The MACS describes a range of manual abilities from level I, where children handle objects easily and successfully, through to level V, where children do not handle objects and are severely limited in their ability to perform simple actions [92].

The *Communication Function Classification Scale* (CFCS) [93] is a five level scale describing the communication ability of individuals with cerebral palsy. The CFCS describes a range of communication abilities from level I, where children are effective senders and receivers with familiar and unfamiliar communication partners, through to level V, where children are seldom effective senders or receivers with familiar communication partners [93].

#### Hypertonia assessment tool

The Hypertonia Assessment Tool (HAT) is a six-item clinical assessment tool used to differentiate between spastic, dystonic and rigid paediatric hypertonia [94]. The HAT allows for standardization of such clinical examination, noting that mixed tone, i.e. both spasticity and dystonia, are present in a large proportion of children with CP [94, 95]. This information will be utilized in subgroup analysis to evaluate whether children with certain hypertonia subtypes demonstrate greater response to intervention than others. In doing so, children with CP can be directed to interventions of greatest efficacy in the future. The HAT has good inter-rater test–retest reliability and validity for the identification of spasticity, and moderate agreement for dystonia [94, 95].

#### Selective control of upper extremity scale

The Selective Control of the Upper Extremity Scale (SCUES) [96] is a measure of selective motor control for the upper limbs. SCUES is a short (< 15 min) video based assessment that is administered by an occupational therapist or physiotherapist. SCUES examines selective motor control for the shoulders, elbow, wrist, and fingers/thumb. The examiner demonstrates a movement, passively moves the child to replicate the movement and determine passive range of motion, then the child replicates the movement. Performance is graded on the presence of mirror movements, movement of additional joints beyond target joint, presence of trunk movement, and the extent to which actual movement is equal to or less than passive range. SCUES has acceptable content validity, intra-rater (> 0.75) and inter-rater (0.72) reliability and construct validity [96].

### Adverse events

Adverse events from intervention and activity based assessment are not anticipated. Adverse events due to imaging aspect of assessment may occur if there is a high degree of anxiety for children about being inside the MRI scanner. Children are not sedated during MRI scans and this research team has developed and piloted a familiarization package to allow children to experience what being inside an MRI scanner is like prior to their consenting to take part in this aspect of the study. The MRI assessment is introduced to children in a standard clinic room with their parents present by the staff members who will be with them on the day of their MRI assessments. All efforts will be made to help children feel comfortable with MRI assessment, however children can withdraw from the MRI assessment if they are experiencing distress and this will not limit their participation in the rest of the study. All adverse events will be reported to the HREC through the chief investigator who will monitor and maintain a register of any adverse events for reporting purposes.

### Statistical methods

As outlined in the CONSORT statement reporting for RCT’s: between group comparisons will be conducted on intention to treat analysis [65]. Missing data arising from incomplete observations and dropouts will be managed using multiple imputations. Multiple imputations is recommended for use in RCT’s because it avoids bias found in last observation carried forward approaches while maintaining power [97].

Summary statistics will be reported for each time point for each group using means and standard deviations. For skewed data, medians and interquartile ranges will be reported.

#### Functional outcome measures

A mixed-effects model with repeated measures will be used to assess within and between group differences. The corresponding baseline measure will be entered as a covariate in the model along with age and somatosensory capacity given these features were used in the randomisation process. The mixed model approach has the advantage of allowing for correlated data (repeated measures) and allows for missing observations within-subject. Model assumptions will be examined and if required transformations applied or non-parametric methods employed. Statistical significance will be set at 0.05.

#### Neuroimaging

##### Functional MRI

First level statistical analyses will contrast blocks (FEEL > REST) on an individual subject basis. Owing to the heterogeneous size and location of brain lesions seen within most cohorts, inter-subject registration (required for voxelwise statistics) may be difficult to perform reliably [98]. We plan to address this by performing region-of-interest analyses that measure the interhemispheric balance of activation between the sensorimotor cortices before and after therapy in the same child. S1, S2, and the dorsolateral prefrontal cortex (as delineated on single-participant templates) will be used. First-level results from all participants will be pooled into an analysis of variance (ANOVA), to investigate (A) changes by time-point, to search for an overall change in brain activation and (B) whether an interaction between time-point and treatment exists.

Task-related fMRI is considered an important neuroimaging modality in researching neuroplasticity. It is however recognised that task-related fMRI presents a “unique set of challenges” [99] that impact data analysis and interpretation. These challenges include but are not limited to: fMRI result variability, inability to distinguish the biological process that underlie changes in activation including alternative explanations such as compensatory activation or strategic shifts, the challenge in presenting task equivalency, and specific challenges in data analysis [99]. Many of these challenges of task-related fMRI are even greater in children with cerebral palsy in comparison to adult populations. As a group, the brain pathology and morphology of children with cerebral palsy is highly heterogeneous and often markedly abnormal owing to the wide range of aetiological processes and the early stage of development at which these processes occur. Additionally, clear relationships between brain structure and a child’s function have been challenging to establish [98]. These factors make standard functional neuroimaging analysis extremely challenging and at risk of limitation in the CP population [100]. Reid et al. make the case that multimodal imaging enables these unique challenges to be addressed and increases the robustness of functional neuroimaging research [99].

This study attempts to reduce the influence of Reid’s cited confounds in a number of ways. First, we have selected long block lengths to reduce effects of abnormal haemodynamic responses. Second, we expect to scan a meaningful number of participants to reduce bias caused by a small number of unusual cases. Third, participants will receive extensive task practice prior to entering the scanner, including in a mock-scanner scenario, reducing differential task anxiety and familiarity between scans. Fourth, we have selected a task with minimal active response required from the participant and should not be substantially more difficult for participants with poorer motor abilities [37, 81]. Fifth, we avoid voxelwise analyses which may be invalidated by pathology. Finally, fMRI analyses will be interpreted in the context of independent clinical scores, measures of cortical thickness, and diffusion measurements of white matter.

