##### Traditional diffusion MRI

Traditional diffusion MRI (dMRI) analysis methods make assumptions about brain structure-function relationships that may not hold in the context of significant brain pathology and cortical reorganisation, as occurs in children with CP [99]. To overcome this challenge, surface-based-fMRI guided tractography will be utilised, as previously demonstrated in children with CP [99], to extract thalamocortical tracts.

Mean FA will be taken for thalamocortical tracts at each time point and entered into an ANOVA to test for (A) the effects of time-point, to test for brain changes, and (B) a time-point – treatment interaction, to test whether treatments evoke different degrees of brain change.

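### Imaging outcomes get an ANOVA with no stated child term or covariates, although the reasons given for the functional mixed model apply equally to the scans

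*Protocol article*

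**What the plan says.** MRI is acquired at four of the five assessments: baseline, end of intervention, 6 months and 12 months (Study protocol, Tables 3 and 4).

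Under Neuroimaging, the Functional MRI section states: "First-level results from all participants will be pooled into an analysis of variance (ANOVA". It sets two tests: (A) change by time-point and (B) time-point by treatment. Traditional diffusion MRI repeats the scheme: "Mean FA will be taken for thalamocortical tracts at each time point and entered into an ANOVA". Neither section names a child term or any covariate.

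Functional outcome measures prescribes a repeated-measures mixed model instead, on the ground that it allows for correlated repeats and for observations missing within a subject. The baseline value is a covariate, "along with age and somatosensory capacity given these features were used in the randomisation process".

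The opening of Statistical methods, placed before the functional and imaging parts divide, sets intention to treat and multiple imputation. Under Adverse events, "children can withdraw from the MRI assessment if they are experiencing distress and this will not limit their participation" in the rest of the study.

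**The concern.** The same children, the same allocation procedure and the same kind of repeated measurement receive two different models, and the article does not say why. Each reason offered for the mixed model holds for imaging. Scans within a child are correlated. MRI is the one assessment a child may stop while staying in the trial, so gaps can be foreseen. Age and severity governed allocation whatever the outcome.

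At stake is the precision of the tests behind hypotheses 2 and 3, with 25 children enrolled per arm. This carries extra weight because Table 1 lists functional MRI among the primary outcomes, although the Abstract and Methods call it secondary.

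**Working it through.** **1. The plan's own figure.** The only sample size given is for the Wrist Position Sense Test: "With an intervention group mean of 15.94 and standard deviation 9.72; and control group mean 25.79 and standard deviation 11.93".
- Pooled SD = sqrt((9.72² + 11.93²)/2) = 10.881.
- Effect size = (25.79 − 15.94)/10.881 = 0.9052, as stated.
- Two-sided 0.05, noncentral t: power is 0.797 at 20 per arm and 0.817 at 21. So 21 per arm (42) reproduces, and 42/0.84 = 50 enrolled.

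The article gives no imaging power, scan-loss rate or within-child correlation. Every rho below is therefore an assumption.

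**2. The two models side by side.**

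| Feature | Functional outcomes | fMRI and FA |
|---|---|---|
| Assessments per child | 5 | 4 |
| Model | Mixed, repeated measures | ANOVA |
| Within-child correlation | Allowed for | Not stated |
| Baseline | Covariate | A level of time |
| Age, severity | Covariates | Not named |
| Missing data | Imputation; model also tolerates gaps | Imputation, by the general rule |

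**3. Cost of not adjusting for baseline.** Take variance σ² at each scan and correlation rho between baseline and a later scan.
- Variance per child of the change score: 2σ²(1 − rho).
- Variance per child after baseline adjustment: σ²(1 − rho²).
- Ratio = (1 − rho²)/(2(1 − rho)) = (1 + rho)/2.
- rho 0.5: 0.75. rho 0.8: 0.90.

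In large-sample terms, 25 adjusted children per arm are worth 25/0.75 = 33.3 or 25/0.90 = 27.8 analysed by change.

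**4. Cost if no child term is fitted.** The interaction is a within-child contrast. Its true residual variance under equal correlation is σ²(1 − rho), but an ANOVA without a child term uses σ². The standard error is too wide by 1/sqrt(1 − rho):
- rho 0.5: 1.41. rho 0.8: 2.24. rho 0.9: 3.16.

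A null simulation (25 per arm, four time points, compound symmetry, 2,000 runs) confirms the direction. At nominal 0.05, the interaction test without a child term rejected in 0.011, 0.0025 and 0.000 of runs at rho 0.3, 0.5 and 0.7. With a child term, rejection was 0.042 to 0.054 across rho 0 to 0.7. The test becomes conservative.

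**5. Age and severity.** With complete data, main effects that are constant over time cancel out of a within-child contrast. Adding only these two terms to the ANOVA would leave test (B) unchanged. They contribute once the comparison is baseline-adjusted, so the functional model is best adopted whole. The documents give no basis for sizing this gain.

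**The case against.** The best defence is that the ANOVA can be read as sound. The Functional MRI section speaks of comparing activation before and after therapy within one child, which suggests repeated measures, and an article may leave the exact form to the analysis plan. The covariate rule sits under a heading for functional outcomes and does not claim to cover imaging. Missing scans are also made less likely by the inclusion and exclusion criteria on MRI tolerance and by mock-scanner preparation. Much of this stands. It does not explain why reasons that apply to both kinds of outcome lead to different models.

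A reader might infer more than the text supports:
- **That every child with a missed scan is dropped, or else correlation is ignored.** The article states neither. A repeated-measures ANOVA on imputed data does neither.
- **That leaving out a baseline covariate is an error.** Baseline is the first level of time, so time-point by treatment already compares change from it.
- **That scan loss would breach the cited minimum, "for at least 20 people per experimental group".** That figure concerns scans before and after intervention, not four scans. At an assumed 90% usable per scan with independent misses, 25 × 0.9² = 20.25 per arm have both, against 25 × 0.9⁴ = 16.4 with all four. Withdrawal driven by the child would also cluster, leaving more complete children than independence implies.
- **That false positives would rise.** Step 4 shows the reverse for the planned interaction test.

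**Conclusion.** The point holds as one of unexplained inconsistency and lost efficiency, not of invalidity. Relative to the functional mixed model, the imaging ANOVA gives up 10% to 25% of the variance of a change comparison (equal variances, assumed rho 0.8 to 0.5). Whether a child term is fitted is not stated. If it is not, the interaction standard error is about 1.4 to 3.2 times too wide (compound symmetry, assumed rho 0.5 to 0.9) and the loss is one of power. The text does not show that the scans will be treated as independent, so this second figure is conditional.

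**What to change.** In Functional MRI and Traditional diffusion MRI, replace the ANOVA with the mixed model already set out under Functional outcome measures, applied to each region-of-interest measure and to tract FA:
- use every available scan, with a child effect or unstructured covariance;
- include visit, treatment, visit by treatment, the baseline value of that measure, age and severity;
- report the adjusted group difference at each post-baseline scan, including time point 2;
- retain test (A). One way is to keep baseline in the outcome vector with a mean common to both arms, in which case baseline enters as an outcome rather than as a covariate.

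State how the general imputation rule applies to missed scans. The mixed model relies on missing at random, which withdrawal through distress may not satisfy, so a sensitivity analysis for MRI withdrawal is advisable.

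The cost is a change of wording and slightly more modelling work on data already being collected.
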